#### Sample size {14}

Due to the lack of clinical trials on the inflammatory effect of nano-curcumin in children with cystic fibrosis, we used HSCRP indices as an effect size. Therefore, the mean ± SD of hs-CRP indices in the curcumin and placebo groups were 5.9 ± 2.57 and 3.6 ± 1.58 respectively [27]. G- power analyzer was applied for calculating sample size between two independent populations with a confidence interval of 95% and power of 80%. By considering 10% dropout and using Deff (deign effect) for stratified sample, a total of 30 samples for each group was calculated. In total, 60 eligible patients with CF are needed to be included for the randomization aspect of this research.

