### Assignment of interventions: allocation

#### Sequence generation {16a}

The patients meeting the inclusion criteria will be enrolled in the study. Initially, stratified randomization will be used to divide the participants into two groups based on disease severity (severe/mild-to-moderate) using spirometry with 40% FEV1 cutoff range. Following that, random sampling will be applied to select the patients from each group to be administered with the nano-curcumin drop or nano-curcumin placebo drop using a random number table (Fig. 1).

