#### Statistical methods for primary and secondary outcomes {20a}

Data analysis will be performed in SPSS version 16, and data distribution will be evaluated using the Kolmogorov-Smirnov test. Data are expressed as frequencies for the qualitative variables, mean and standard deviation for the normally distributed continuous variables, and median and interquartile range for the other variables. In addition, intergroup differences will be evaluated using paired t-test for the normally distributed continuous variables and Wilcoxon rank-sum test for the other variables. Intragroup differences will be assessed using independent *t* test for the normally distributed continuous variables and Mann-Whitney *U* test for the other variables. The mean changes in the secondary outcomes will also be adjusted for the baseline data and disease severity using the analysis of covariance (ANCOVA). In all the statistical analyses, the *P* value of ≤ 0.05 will be considered significant.

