#### Methods for additional analyses (e.g., subgroup analyses) {20b}

The baseline data and disease severity will be controlled using ANCOVA or binary logistic regression.

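### The primary biomarkers get an unadjusted test picked by a normality check; baseline- and severity-adjusted ANCOVA is tied to the secondary outcomes and otherwise left without scope or rank

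*Protocol article*

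**What the plan says.** Outcomes {12} defines the primary outcomes as changes from baseline to 3 months in IL-6, IL-10, hs-CRP, swab neutrophil count and culture, and fecal calprotectin. Participant timeline {13} has primary and secondary outcomes measured before treatment and at 3 months. Under Sequence generation {16a}, "stratified randomization will be used to divide the participants into two groups based on disease severity", with a 40% FEV1 cutoff.

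Section {20a} covers both classes of outcome. First, "data distribution will be evaluated using the Kolmogorov-Smirnov test". Normal continuous variables then get a t-type test and the others a rank test. The only adjusted analysis in that section is attached to one class: "The mean changes in the secondary outcomes will also be adjusted for the baseline data and disease severity using the analysis of covariance (ANCOVA").

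Section {20b}, on additional analyses, adds: "The baseline data and disease severity will be controlled using ANCOVA or binary logistic regression". It names no outcome and does not rank this analysis against the one in {20a}.

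**The concern.** The analysis best suited to a baseline-measured outcome in a severity-stratified trial is already planned, but {20a} gives it to the secondary outcomes. Three things follow.

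- The primary comparison forgoes the precision that the baseline value and the stratum would give, and chance baseline differences stay in the estimate or are handled less efficiently.
- Because a normality check picks the test, the quantity compared (a mean difference or a rank ordering) depends on the data and may differ between IL-6, IL-10, hs-CRP and calprotectin.
- If {20b} does reach the primary outcomes, each marker can yield an unadjusted and an adjusted answer with no rule for which is the result.

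**Working it through.** **1. The plan's own sample size.** Sample size {14} gives: "the mean ± SD of hs-CRP indices in the curcumin and placebo groups were 5.9 ± 2.57 and 3.6 ± 1.58 respectively"; a calculation "with a confidence interval of 95% and power of 80" percent; and "By considering 10% dropout and using Deff (deign effect) for stratified sample, a total of 30 samples for each group was calculated". Two-sided testing is assumed, since sidedness is not stated.

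- Pooled SD = √[(2.57² + 1.58²)/2] = 2.133. Standardised difference = (5.9 − 3.6)/2.133 = 1.078.
- n per arm = 2(1.960 + 0.842)²/1.078² = 13.5, so 14 (15 by the noncentral t).
- With 10% dropout: 14/0.9 gives 16, and 15/0.9 gives 17.
- Reaching 30 needs a design effect of about 30 × 0.9/15 = 1.80 to 30 × 0.9/14 = 1.93. The value used is not stated, so 30 cannot be reproduced, but it cannot be called wrong either.
- Completers per arm: 30 × 0.9 = 27. At 1.078 SD the unadjusted t-test then has about 97% power.

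**2. Precision given up.** Take the follow-up SD as 1, the same SD at both visits, a linear relation, and correlation rho between baseline and month 3. Variances per patient:

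- change score: 2(1 − rho)
- ANCOVA: 1 − rho²
- ratio: (1 − rho²)/[2(1 − rho)] = (1 + rho)/2

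The protocol gives no rho; 0.2 to 0.8 is an assumed range. With 27 per arm, two-sided 5%, noncentral t, and effects in follow-up SD units:

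| rho | Variance, change | Variance, ANCOVA | Ratio | Detectable at 80% power, change vs ANCOVA | Power at 0.5 SD, change vs ANCOVA |
|---|---|---|---|---|---|
| 0.2 | 1.60 | 0.96 | 0.60 | 0.98 vs 0.76 | 30% vs 45% |
| 0.5 | 1.00 | 0.75 | 0.75 | 0.78 vs 0.67 | 44% vs 55% |
| 0.8 | 0.40 | 0.36 | 0.90 | 0.49 vs 0.47 | 81% vs 85% |

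Put as patients, 27 per arm under ANCOVA match 27/0.60 = 45, 27/0.75 = 36 or 27/0.90 = 30 per arm under a change-score test. If the test were instead applied to month-3 values alone, the ratio would be 1 − rho²: 0.96, 0.75 and 0.36. Neither ratio describes the rank-test branch.

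**3. Leaving out the stratum.** A simulation used 60 patients, arms balanced within each stratum, no treatment effect, a 1 SD severity effect (assumed) and 20,000 runs. Actual type I error at nominal 0.05:

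| Share severe (assumed) | Unadjusted t-test | Stratum-adjusted |
|---|---|---|
| 20% | 0.032 | 0.049 |
| 30% | 0.033 | 0.051 |
| 50% | 0.027 | 0.047 |

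The test errs on the safe side and pays in power. {16a} does not mention blocking. If balance within strata is not forced, the unadjusted test stays near its nominal level, and severity simply adds noise.

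**4. Which test {20a} names.** As written, it assigns the paired t-test to intergroup differences, and the independent t-test and Mann-Whitney test to intragroup differences. These labels are reversed. Steps 2 and 3 assume that a two-sample test is meant between groups; read literally, the normal-data branch names a test that does not fit two independent arms.

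**5. Whether the log scale suits every marker.** Table 2 gives IL-6 a detection limit of 2 pg/ml against a normal range up to 1.8, so any normal IL-6 value is undetectable. IL-10 has a limit of 2 pg/ml against a range of 1.2–7.8. The normal swab cell count is up to 2–3, so zeros are possible and their logarithm is undefined.

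**The case against.** A reader might infer that the primary outcomes get no adjustment at all and that the stratification factor is ignored. The document does not support that. Section {20b} plans control for baseline and severity without limiting it to secondary outcomes. Its logistic option points towards the primary outcomes, because spirometry, BMI z-score and the questionnaire are continuous as measured, whereas culture, a primary outcome, is naturally binary. What remains is that this adjustment is neither assigned to named outcomes nor ranked.

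A reader might also infer that the unadjusted comparison is biased or inflates type I error. It does not: a two-sample test is valid under randomisation, and omitting a balanced prognostic stratum makes the t-test conservative.

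The gain should not be oversold either. It is small at high rho (0.49 vs 0.47 SD at rho 0.8), and the unadjusted test already has about 97% power at the planning effect. Both points stand. But {14} takes that effect from another study precisely because trials in children with CF are lacking, and it gives no effect for the other markers. Precision therefore matters if true effects are smaller.

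Finally, ranking analyses and choosing transformations can be left to an analysis plan that is not shown. That would answer silence, but {20a} makes an explicit assignment, and it gives the adjusted analysis to the secondary outcomes.

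**Conclusion.** The point holds as one of efficiency and clarity, and the plan should be changed. Section {20a} leaves the primary biomarkers to an unadjusted test selected by a normality check and ties adjusted ANCOVA to the secondary outcomes; {20b} leaves the scope and standing of adjustment open.

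Against a change-score t-test, ANCOVA removes between 40% and 10% of the variance for rho from 0.2 to 0.8. This rests on an assumed rho, equal SDs at both visits and the parametric branch. The stratum result rests on an assumed severity effect, an assumed share of severe patients and balance within strata. Since {10} requires FEV1 of at least 30%, the severe stratum covers only 30% to 40% and may be small, which would limit what the severity term adds. That the concentrations are skewed is an expectation, not something the document shows.

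**What to change.** Reconcile {20a} and {20b} in one statement of the primary analysis:

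- For each continuous primary biomarker, one pre-specified ANCOVA of the month-3 value on treatment, baseline value and FEV1 stratum (40% cutoff). Use the log scale for skewed concentrations, reported as a geometric mean ratio with 95% CI, with a stated rule for values below the detection limit.
- Where non-detects or zeros are common (IL-6, IL-10, neutrophil count), a rank-based ANCOVA or a suitable count model with the same covariates, chosen in advance for each marker.
- For culture, confirm that the logistic regression in {20b} with these covariates is the primary analysis.
- Drop the Kolmogorov-Smirnov switch and keep the unadjusted rank test as a sensitivity analysis.
- Correct the reversed intergroup and intragroup test labels.

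This needs no extra patients, visits or measurements, because baseline values and FEV1 stratum are already collected. It does need more than a change of wording: someone must decide, before the data are seen, how non-detects and zeros are handled for each marker.

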#### Interim analyses {21b}

Interim analysis is not considered. In case of frequent side effects (more than previous reports), we will stop the intervention and present the results to the Ethics Committee of Mashhad University of Medical Sciences (MUMS) for further decision

#### Methods for additional analyses (e.g., subgroup analyses) {20b}

The baseline data and disease severity will be controlled using ANCOVA or binary logistic regression.

#### Analytical method to handle protocol non-adherence and any statistical methods to handle missing data {20c}

In order to incorporate the outcome data of the participants into data analysis regardless of the protocol adherence, all the analyses will be performed in accordance with the intention-to-treat principle. The final observation by the forward method will also be used to impute the missing data for the intention-to-treat analysis.

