**Methods:**

This prospective, double blind control trial will be conducted at the Akbar Children’s Hospital in Mashhad, Iran. Children with CF will be enrolled based on the eligibility criteria. Placebo and curcumin with the maximum dose of 80 mg considering the body surface of the patients will be administrated for 3 months. The primary outcome is to evaluate inflammation based on serum interleukin-6, interleukin-10, and hs-CRP, stool calprotectin, and neutrophil count of nasopharyngeal swab. The secondary outcome involved clinical assessment via spirometry, anthropometrics, and quality of life. They will be assessed before and after 3 months.

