#### Criteria for discontinuing or modifying allocated interventions {11b}

Although no special side effect has been reported until now, with any intervention-related side effects, we will stop the intervention and report it to the Ethics committee of Mashhad University of Medical Sciences (MUMS) for decision making. If the participants request to discontinue treatment or report the deterioration of their condition due to CF, we will stop the intervention.

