#### Participant timeline {13}

Nutritional recommendations will be provided to all the patients and/or their parents and legal guardians stand on the CF requirements and adjustable CREON dosing to the level of dietary fat. In addition, the patients and their parents completed the CFQ depend on age.

Anthropometric measurements (weight and height) will be performed using a digital scale (model: SECA). Body weight will be measured without shoes, and height will be measured in the standing position without shoes with the heels stuck to the wall and the head looking frontwards with the accuracy of 0.5 cm.

The fecal examination will be performed before and after the intervention. Before intervention, fecal sample will be evaluated for bacterial over growth and parasite specially giardia by checking stool PH and trophozoites or cysts of giardia. Any positive result will be treated with antibiotics before stating the trials.

Blood sampling will be performed before and after the intervention. Approximately 5 mL of blood will be collected, immediately centrifuged, with the serum separated from the sediment, and preserved at the minimum of temperature of − 20 °C.

The primary and secondary consequences of the treatment will be investigated before and 3 months after the treatment. The clinical evaluation and follow-up of medication use and side effects will also be carried out via phone call and paying monthly visit to the clinic, and the findings will privately be presented to the patients (Table 2).

**Table 2 Tab2:** Laboratory measurements, equipment, and normal range

Test	Test equipment	Company	Quality control	Normal range
**Hs-CRP**	Biochemical auto analyzer	Pars azmoon	Intra-assay CV: 2.2% Inter-assay CV: 1.1% Linearity (*R*^2^): 0.99 Detection limit: 0.1 mg/lit	Children: up 2.8 mg/L Adult: up to 5 mg/L
**IL-6**	ELISA kit	Demeditec	Intra assay CV: 4.2% Inter assay CV: 4.9% Accuracy: 99% Specificity: 94% Detection limit: 2 pg/ml	Up to 1.8 pg/ml
**IL-10**	ELISA kit	pars gene (Invitrogen)	Intra assay CV < 3% Inter assay CV < 8% Detection limit:2 pg/ml	1.2–7.8 pg/ml
**Calprotectin**	ELISA kit	EUROIMMUN	Intra assay CV: 3.4% Inter assay CV: 6.4% Linearity(*R*^2^): 0.99 Sensitivity: 94.1% Specificity: 95.5% Detection limit:1.9 μg/g	50–120 μg/g: borderline > 120 μg/g: positive
**Nasopharyngeal swab**	URT-S&C (gram-positive, gram negative, pseudomonas)	Variable		Culture: negative WBC count: up to 2–3

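### With outcomes measured only at baseline and month 3, last observation carried forward records every child without a month-3 value as having changed by exactly zero

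*Protocol article*

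**What the plan says.** Section {20c} of the protocol article commits all analyses to the intention-to-treat principle, using outcome data whatever the adherence. It then fixes the handling of missing values: "The final observation by the forward method will also be used to impute the missing data for the intention-to-treat analysis". The wording is loose, but LOCF is the only plausible reading. No other method is named.

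The measurement schedule is in section {13}: "The primary and secondary consequences of the treatment will be investigated before and 3 months after the treatment". The same section says of the samples behind the biomarkers that "Blood sampling will be performed before and after the intervention" and "The fecal examination will be performed before and after the intervention". The abstract agrees: "They will be assessed before and after 3 months".

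There are monthly contacts, but their content is different: "The clinical evaluation and follow-up of medication use and side effects will also be carried out via phone call" and at clinic visits. No biomarker, spirometry, BMI or quality-of-life assessment is scheduled there. The schedule table is not shown in the text available, but the prose is explicit for both primary and secondary outcomes.

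On stopping, section {11b} says: "If the participants request to discontinue treatment or report the deterioration of their condition due to CF, we will stop the intervention".

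**The concern.** LOCF is usually discussed for trials with several post-baseline visits, where the carried value at least reflects some time on treatment. Here there is none, so LOCF becomes baseline carried forward. The primary outcomes in section {12} are changes from baseline to 3 months, so the rule fills in the endpoint itself with a zero that nobody measured.

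Two things are at stake. The estimated difference depends on how many children are missing in each arm, and not only on what the treatment does. The invented zeros also enter the tests and standard errors as if they were data. Because section {20c} covers all the analyses, every outcome with a missing month-3 value is affected. With 30 children per arm, a few such values are not negligible.

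**Working it through.** **Inputs from the protocol, section {14}.** hs-CRP means 5.9 and 3.6, a difference of 2.3; SDs 2.57 and 1.58; 10% dropout; 30 per group. No unit is given for the 2.3, so none is used here.

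Pooled SD = √[(2.57² + 1.58²)/2] = 2.13. Expected missing children = 10% × 30 = 3 per arm.

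The planned 30 per group cannot be reproduced. A two-sided 5% t-test with 80% power needs 15 per group, or 17 after 10% dropout, and reaching 30 takes a design effect of about 1.8, a value that the protocol does not give. Nothing below depends on this.

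**Assumptions.** The 2.3 is treated as a difference in mean change and 2.13 as the SD of change; section {14} does not say that they are. Dropout other than 10%, and any split between arms, is assumed.

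**Step 1: what LOCF does.** If the month-3 value is missing, it is set to the baseline value, so change = 0. In an arm with missing share q and mean change m among the observed children, the analysed mean is (1 - q) × m.

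**Step 2: equal, non-informative dropout.** The difference is multiplied by (1 - q).

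| Dropout in both arms | Analysed difference |
|---|---|
| 5% (assumed) | 0.95 × 2.3 = 2.19 |
| 10% (protocol) | 0.90 × 2.3 = 2.07 |
| 20% (assumed) | 0.80 × 2.3 = 1.84 |
| 30% (assumed) | 0.70 × 2.3 = 1.61 |

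**Step 3: unequal dropout, no treatment effect.** If both arms truly change by c, the analysed difference is (1 - q₁)c - (1 - q₂)c. With c = -2, q₁ = 5% and q₂ = 20% (all assumed): 0.95 × (-2) - 0.80 × (-2) = -1.90 + 1.60 = -0.30. The true difference is zero. The observed children alone would give zero on average, because dropout here is unrelated to outcome.

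**Step 4: apparent precision.** Take one arm of 30 with mean change -2.3, SD 2.13 and 20% missing (assumed).

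- SD with imputed zeros = √(0.80 × 2.13² + 0.20 × 0.80 × 2.3²) = √(3.630 + 0.846) = 2.116. Standard error = 2.116/√30 = 0.386.
- Standard error from the 24 children measured = 2.13/√24 = 0.435.
- Standard error had all 30 been measured = 2.13/√30 = 0.389.

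So losing 6 of 30 children leaves a standard error no larger than complete data would give.

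**The case against.** **Size at the planned dropout.** About three children per arm are expected to be missing, and a fall from 2.3 to 2.07 is conservative. On the protocol's own figures (SD 2.13 held fixed, two-sided 5% t-test, 30 per arm) power is still about 96% at 2.07 and about 91% at 1.84. This stands, and it limits the seriousness of the point. It does not rescue the estimate, and it does not cover unequal dropout.

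**Deterioration and missingness.** A reader might infer that children who deteriorate leave the trial and are then recorded as unchanged, so that LOCF hides harm. The documents do not support that as a statement of fact. Section {11b} stops the intervention, not follow-up. Section {20c} intends to use outcome data regardless of adherence. Section {18b} plans regular phone contact or free visits to support retention. A child who stops the drops and is measured at month 3 contributes a real value and is never imputed. What remains is that no sentence expressly promises month-3 sampling after stopping, so a link between deterioration and missing data is possible but not shown.

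**Informative dropout as evidence against LOCF.** This does not separate the methods in the way one might expect. Suppose a true harm of +1 (changes with SD 2.13 and means +1 and 0), with every child above +2.5 missing, about 24% and 12% of the arms. LOCF then gives +0.52 and the observed children alone +0.61. Of the 0.48 lost, 0.39 comes from the assumed selection and only 0.09 from LOCF.

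The ordering can also reverse. Suppose 20% are missing on active and none on placebo, observed changes are -2.3 and 0, and the missing children truly worsen by 1. The truth is 0.80 × (-2.3) + 0.20 × 1 = -1.64. LOCF gives -1.84 and the observed children -2.30. A missing-at-random analysis does not cure informative dropout, which is why the fix includes a sensitivity analysis.

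**What the analysis plan may hold.** Sensitivity analyses are often left to an analysis plan that is not shown, so their absence is not the point. The point is the imputation rule that the protocol does state.

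**Conclusion.** The point holds, and it follows from sections {20c} and {13} read together: a missing month-3 value becomes a change of exactly zero. It concerns children with a baseline value only; a missing baseline has nothing to carry forward.

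At the protocol's 10% dropout, equal between arms and unrelated to outcome, the planned difference loses a tenth (0.23). Unequal dropout combined with a change common to both arms can create a difference, 0.30 in the assumed example. Precision is overstated, with a per-arm standard error of 0.386 against 0.435 at an assumed 20% dropout.

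The direction and size of bias in the actual trial cannot be known from the documents. It may be towards or away from no effect, so LOCF cannot be defended as reliably conservative. No claim is made that deteriorating children will be missing. This should be fixed before any unblinded analysis, but at the expected dropout it does not threaten the trial as a whole.

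**What to change.** 1. In section {20c}, replace LOCF. As the main analysis, use ANCOVA on observed month-3 values, adjusted for baseline value and disease severity, or multiple imputation by arm. State that this assumes data missing at random. ANCOVA with these covariates is already named in sections {20a} and {20b}. With two time points, it would do much the same as multiple imputation unless other variables predict the outcome well.
2. Add one delta-adjusted sensitivity analysis that assumes worse values in children with missing month-3 data, because missing-at-random methods do not correct informative dropout. Fix the range of deltas in advance; section {17a} says that the data analysts are not blinded.
3. State in section {20c} that children who stop the drops are still measured at the scheduled month-3 visit, in line with its intention-to-treat commitment. This changes follow-up wording only, not the rule for stopping treatment.

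The cost is a change of wording and slightly more analysis. No new visit, sample or participant is needed. Multiple imputation, if chosen, may need an add-on to the SPSS version 16 named in section {20a}, or another package.
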